### Participants and recruitment

Adult patients who are undergoing surgery for a degenerative condition of the lumbar spine (lumbar spinal stenosis, spondylolisthesis or degenerative disc disease) using any kind of surgical decompression (laminectomy, hemilaminectomy, foraminotomy, with open or minimally invasive technique) associated with fusion, and able to read and speak Italian (site in southern Switzerland) or Dutch (site in the Netherlands) will be eligible for inclusion. One hundred and fifty patients will be enrolled at the outpatient clinic of the Department of Neurosurgery, Neurocenter of Southern Switzerland, Regional Hospital of Lugano, Lugano, Switzerland (Site 1) and the Department of Neurosurgery of Zuyderland Medical Center, Heerlen, The Netherlands (Site 2). All patients entering the screening phase will be registered on a Patient Registration Log and a unique registration number will be assigned. Clinical data will be assessed to evaluate a subject’s eligibility.

Patients will be excluded from the study if they meet any of the following criteria:
Plans to undergo major surgery within six months after current lumbar spinal fusion surgeryComorbid severe psychiatric conditions such as schizophrenia or personality disorderKnown or suspected non-compliance, drug or alcohol abuseInability to follow the procedures of the study, e.g. due to dementiaThe presence of any serious medical comorbidity such as sepsis or cancer that might cause disability or worsen the patient’s general health conditionPregnancyAn opioid intrathecal pumpPrisoners

Patients eligible for participation will be evaluated at least 6 weeks before surgery and asked for informed consent, and then to complete the PCS [23]. Patients with high pain catastrophizing, defined as a score of ≥24 on the PCS, will be eligible for randomization to perioperative treatment with CBT or educational program. This cut-off was initially based on a previous study in whiplash patients that showed that a pretreatment score of 24 or higher on the PCS best predicted follow-up pain ratings and work status after multidisciplinary treatment [24]. More recently, Tuna et al. [16] suggested an almost identical cut-off for the PCS (i.e. > 24) to obtain the highest sensitivity and specificity to predict unfavorable outcome after spine surgery, defined by as score on the Oswestry Disability Index (ODI) of 20 or higher.

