A non-randomized group, consisting of low catastrophizing patients (score < 24 PCS), will be included as an observational cohort. These patients will not undergo any additional intervention besides usual care but will undergo the same data-collection as the high catastrophizing randomized groups.

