#### Educational program plus progressive exercise program

The control intervention consists of biomedical and surgery-specific education before surgery and an exercise manual after surgery. To control for differences in attention between the two interventions, patients in the educational program will also have two meetings before and four meetings after surgery with members of the research team (in person or through telephone).

The pre-surgical, biomedical and surgery-specific education is based on a previously developed educational intervention for spinal patients [26]. In the first preoperative in person meeting (30–45 min), a ‘not-blinded’ neurosurgeon will provide verbal information on the preparation for surgery, surgery itself and recovery from surgery, stressing the importance of postoperative exercises. Questions raised by the patient are discussed. A booklet is provided with information about the following topics: structure of the spinal column and spinal diseases; examinations before surgery; the operative environment; surgical procedures; anesthetic procedures; postoperative care and postoperative pain reduction. A second telephone meeting a second telephone meeting of 10–15 min with the same neurosurgeon is planned 1–2 weeks after to answer question about the given information and to discuss point that are unclear.

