### Outcome measures

Primary and secondary outcomes will be measured at baseline preoperatively and 2, 6 and 12 months after surgery (Table 2). Investigators and research assistants collecting outcomes from patients at different time points during follow-up will be blinded to group assignment. The psychologists delivering the CBT and the clinicians providing the educational program to the control group cannot be blinded. Nevertheless, patients will be blinded to the study hypotheses and will be informed that the study is examining the comparative benefits of two treatments that are given in addition to usual care and that may potentially improve outcomes. The patients will not be informed about the likely association between a high PCS score and lower outcomes after spinal fusion surgery, neither about the fact that the control intervention will not address catastrophizing.

**Table 2 Tab2:** Outcome measures. (Days-D, Weeks-W, Months-M)

***Outcomes***	***Instrument***	***Study Period***	***Enrollment***		***Surgery***					
		***Time***	***≥ 6 W***	***Intervention*** ***Between 4 W preop***	***Baseline***	***4D***	***Intervention*** ***Between 8 W postop***	***8 W***	***6 M***	***12 M***
*Primary outcome:*										
Self-reported function	COMI		X					X	X	X
*Secondary outcomes:*										
Self-reported Pain intensity	NRS		X			X		X	X	X
Self-reported disability	ODI		X					X	X	X
Self-reported daily-function and quality of life	EQ-5D		X					X	X	X
Self-reported mood and cognition	PROMIS depression		X					X	X	X
Patient’s global impression of change	PGIC		X					X	X	X
Self-reported pain catastrophizing	PCS		X					X	X	X
Medication Usage	MQS		X					X	X	X
Work productivity and activity impairment	WPAI:LBP		X					X	X	X
*Other variables:*										
Patient demographics	Medical record		X							
Surgical complications	Clavien-Dindo							X		
Self-reported anxiety	PROMIS anxiety		X					X	X	X
Self-reported fear of surgery	SFQ		X					X	X	X
Self-reported fear avoidance beliefs	FABQpa		X					X	X	X

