All patients randomized (i.e. those with a PCS score > 24) will be analyzed in an intention-to-treat analysis. To test for a difference between the CBT and control group in the COMI at 12 months, linear regression will be used, with correction for baseline COMI and center. In addition, the difference in the trajectory of COMI over time will be assessed by means of linear mixed-effects regression, taking all follow-up measurements into account. Adjustment for center, type of surgery, age and gender will be made and, if necessary, for other prognostic variables significantly associated with the outcome (i.e., acute postoperative pain intensity, severity of catastrophizing, preoperative depression, preoperative surgical fear, length of current sick leave, pain duration). Stepwise backward elimination using the Wald test will be used to select prognostic variables significantly associated with the outcome. Any control variables that are incomplete will be imputed if the proportion of incomplete patients exceeds 0.05. We will use multiple imputation with fully conditional specification with the number of imputations set to the percentage of incomplete patients. Predictive mean matching will be used to draw values to be imputed. Secondary outcome variables will be analyzed similar to the primary outcome. For these, logistic regression analysis adjusted for center will be used to test for differences in proportions at 12 months postoperatively.

Exploratory, we will compare the outcomes of the patients in the two intervention groups with the outcomes of patients with low pain catastrophizing scores (i.e. those with a PCS score < 24) undergoing care as usual. Linear mixed-effects regression for the three groups will be performed with primary and secondary outcomes at the three postoperative assessment periods and controlling for preoperative values. This analysis will indicate whether high catastrophizing patients follow a similar trajectory of pain and functioning after spinal fusion surgery compared non-catastrophizing patients.

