There are some limitations of our study protocol that should be mentioned. The main limitation is patient’s compliance to the intervention. In fact, very few data exist that analyze the impact and feasibility of CBT in the perioperative period after spinal fusion surgery. Another possible limitation is related to potential differences in levels of catastrophizing between the populations of the two centers. Moreover, the exact proportion of high catastrophizing patients (defined in this study as having a PCS ≥ 24) is not known in advance and could vary between the two centers. Additionally, a potential weakness of our study protocol is related to the control condition, conceived to reduce patient’s expectation bias, augmenting contact time and attention, and therefore reducing non-specific effects on outcome. It is well known in psychological research that expectation is one of the most important non-specific factors that may modulate patients outcomes [61]. However, it is difficult to know if this intervention will control for other non-specific factors that could be present (e.g. patient motivation or the therapeutic relationship between the psychologist and patients during CBT). Additionally, because of the difference in length of sessions between the CBT sessions and the education program (the latter being of a shorter duration) the factor of ‘contact time’ is not perfectly controlled for. On the other hand, the first educational session and post-discharge educational session will be held ‘face to face’ whereas all CBT sessions will be delivered by video teleconference. This ‘in-person attention’ in the two educational sessions might compensate for the shorter contact time in the control group in comparison to the CBT group.

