Furthermore, this study can demonstrate efficacy of the CBT intervention for high catastrophizing patients, but it does not assess cost-effectiveness. Although some cost elements are included (medication use, further treatment, employment status), no full cost analyses will be conducted. Moreover, if this study shows a positive effect on pain and disability from perioperative CBT, this will not clarify the optimal dosage of the intervention or the ideal timing. Finally, it cannot clarify whether a PCS score of 24 or higher is the most optimal cut-off for offering patients CBT. Future studies should conduct sensitivity analyses to establish at which level of pain catastrophizing intervention should be offered, to come to an optimal cost-benefit ratio.

In conclusion, the results of this study are expected to provide valuable information that will potentially change clinical practice of lumbar spinal fusion surgery. If our study can demonstrate that perioperative CBT is effective in improving clinical outcome after lumbar spine fusion surgery in high catastrophizing patients, it is highly recommended to perform prescreening to identify this subgroup for which a perioperative psychological treatment will be indicated. If CBT will not prove to be superior and if this study will confirm that high levels of pain catastrophizing have a negative impact on clinical outcome, that might be a reason to be very reluctant in offering these patients a spinal fusion procedure, trying to opt for less invasive treatment options.

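### The design cannot support the Discussion's inference about offering fusion: everyone has fusion, and high catastrophizing coincides fully with added care

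*Protocol article*

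**What the plan says.** **Who receives what.** Under Participants and recruitment, all participants are having decompression with fusion. Patients with a PCS score of 24 or more "will be eligible for randomization to perioperative treatment with CBT or educational program". Under Outcome measures, these are described to patients as "two treatments that are given in addition to usual care". The control arm is itself a programme: "patients in the educational program will also have two meetings before and four meetings after surgery with members of the research team".

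**The low-PCS cohort.** "A non-randomized group, consisting of low catastrophizing patients (score < 24 PCS), will be included as an observational cohort". For this cohort, "These patients will not undergo any additional intervention besides usual care".

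**The analysis.** Power considerations and statistical analysis labels the high-versus-low comparison exploratory. A linear mixed model for the three groups "will be performed with primary and secondary outcomes at the three postoperative assessment periods and controlling for preoperative values". The primary linear regression, by contrast, corrects for baseline COMI and centre.

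**The interpretation.** The Discussion wants to see whether CBT brings high-PCS patients to the improvement expected in low-PCS patients. It warns that the proportion of high-PCS patients "is not known in advance and could vary between the two centers". It closes by saying that if CBT is not superior and a negative impact of catastrophizing is confirmed, "that might be a reason to be very reluctant in offering these patients a spinal fusion procedure", and less invasive options might be sought.

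**The concern.** The closing inference has two premises: CBT does not beat the control, and high catastrophizing worsens outcome. Neither leads to a statement about offering fusion, because no participant goes without it. The second premise is also not cleanly estimable, because PCS level and added care are the same variable in this design.

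Two readings of the results are at stake. A null CBT result together with a high-versus-low gap could be cited on whether a group of patients should be offered an operation, although the trial contains no such comparison. Conversely, a small gap between the CBT arm and the low-PCS cohort could be credited to CBT when the added contact and attention, or a different centre mix, would explain it. The Discussion lists several limitations (compliance, contact time, the cut-off, costs) but neither the missing non-fusion comparator nor the missing high-PCS usual-care group.

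**Working it through.** **1. The plan's own figure.** Inputs from Power considerations and statistical analysis: difference 2 COMI points, SD 2.5 (d = 2/2.5 = 0.80), type-I error 0.05 (taken as two-sided), power 0.95. The t-test calculation gives 41.6, so 42 per group, with power 0.952. Dropout: 42/0.85 = 49.4, so 50 per group, and 3 × 50 = 150. The stated sample size reproduces; arithmetic is not the problem.

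**2. Who gets what.**

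| Group | Fusion | Added programme |
|---|---|---|
| High PCS, CBT | all | CBT, six sessions |
| High PCS, control | all | education plus exercise, six meetings |
| Low PCS | all | none |

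Two cells are empty: high PCS with usual care only, and any patient without fusion.

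**3. What the high-versus-low contrast estimates.** Higher COMI is worse. Let c be the increase in COMI due to high catastrophizing and x the reduction due to the added programme, taken as additive. The expected high-minus-low difference is c − x. The documents give no value for x, so a range of −1 to 2 points is assumed. Power is from a two-sided t-test with 42 per group and SD 2.5, and is indicative only, since the planned model is a mixed model with baseline adjustment.

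| True c | Assumed x | Expected difference c − x | Probability of p < 0.05 |
|---|---|---|---|
| 2 | 0 | 2.0 | 0.95 |
| 2 | 0.5 | 1.5 | 0.78 |
| 2 | 1 | 1.0 | 0.44 |
| 2 | 2 | 0 | 0.05 |
| 0 | 1 | −1.0 (high PCS looks better) | 0.44 |
| 0 | −1 | 1.0 (high PCS looks worse) | 0.44 |

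More patients would estimate c − x more precisely but would not separate c from x.

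**4. Crediting CBT with closing the gap.** Write x_C for the benefit of CBT and x_E for that of education plus exercise, each against usual care. CBT versus low estimates c − x_C; control versus low estimates c − x_E. If x_C = x_E = c, the CBT arm reaches the low-PCS level although CBT adds nothing over the control. Subtracting, (c − x_E) − (c − x_C) = x_C − x_E, which is the randomised contrast. Only that quantity is specific to CBT.

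**5. Fusion against a less invasive option.** For high-PCS patients the benefit of fusion is B = (mean score with the alternative) − (mean score with fusion). The trial supplies the second term only. Whatever the high-versus-low gap after fusion, B can take any value: patients with a worse prognosis may do worse under either treatment. CBT failing to beat an active control adds nothing about the missing term.

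**6. Centre.** If the share of patients from one centre is p_H in the high-PCS groups and p_L in the low-PCS cohort, and the centres differ in outcome by D after baseline adjustment, a model without centre carries a bias of (p_H − p_L) × D. The documents give none of these values, but the Discussion says the high-PCS share could differ between centres, so p_H = p_L cannot be assumed. Centre-stratified randomisation balances the two randomised arms only.

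**The case against.** The strongest reply is that the sentence is a hedged closing remark with two conditions, not an objective, hypothesis or decision rule. The aim, primary outcome and primary analysis concern CBT versus control in high-PCS patients. The active control is a deliberate, explained choice to isolate CBT from attention and contact. The cohort is labelled non-randomised and its analysis exploratory, and both intervention groups are to be compared with it, so control-versus-low will stand beside CBT-versus-low. All of this stands. It limits the weight of the point but does not supply the missing comparators.

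Second, the confounding is not necessarily fatal to a prognostic reading. If the added care helps or is neutral, it shrinks the gap, so a clear high-PCS deficit would still suggest an association. Severity of catastrophizing is also a candidate covariate within the randomised arms, though only above the cut-off. This stands too, with the direction of x as an assumption. A reader might infer that the trial can say nothing about catastrophizing and outcome; that is too strong.

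Third, the covariates of the three-group model are given in one summary sentence, and a full list may sit elsewhere. That is fair: centre is not named there, which is not the same as being excluded. Naming it is still worthwhile, since the article names it for the primary model and flags the centre difference itself.

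A reader might also infer that low-PCS patients will be enrolled earlier than randomised patients, so that calendar time is confounded too. The article states no enrolment pace for the cohort, so this is not supported and forms no part of the point.

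**Conclusion.** The point holds for the interpretation, not for the trial's main test. The inference about offering fusion rests on a contrast that the design cannot estimate at any sample size. The high-versus-low comparison mixes the effect of catastrophizing with that of the added programme, and the overlap is complete: no high-PCS patient receives usual care alone. How far this distorts the gap depends on x, which is unknown; the figures above rest on an assumed range, additive effects, SD 2.5 and 42 per group. A non-randomised prognostic association remains a legitimate result.

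A reader might take the closing sentence as a planned decision to withhold surgery, or conclude that the whole trial is compromised. The documents support neither: the wording is conditional, and the randomised CBT-versus-control comparison is untouched. The text and the exploratory model should be corrected, because the Discussion presents the results as potentially practice-changing.

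**What to change.** 1. Remove the inference about offering fusion. Describe any high-versus-low difference as a non-randomised prognostic association after fusion, and state the missing non-fusion comparator and the missing high-PCS usual-care group as limitations.
2. State that any closing of the gap to the low-PCS level is attributed to CBT only through the randomised CBT-versus-control contrast. The planned comparisons already provide the numbers; only the rule of interpretation is new.
3. Name centre as a covariate in the three-group mixed model, alongside the preoperative values.

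The cost is wording and one model term, with no extra patients. The downside is that the exploratory cohort supports a narrower claim. For scale, a high-PCS usual-care group of the same size would add 42/0.85 = 49.4, so 50 patients (4 × 50 = 200 instead of 150). It would remove the overlap with added care but would still give no evidence on fusion against an alternative, so it is not proposed here.

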## Trial status

Participant recruitment started in February 2020 and is planned to continue until November 2022. An interim analysis is planned after 6 months follow up of 21 patients. It is expected that data regarding the intervention effects will be available at the end of 2023.

## Data Availability

No data has been collected yet. All methods/questionnaires have been described in the study protocol.

## Abbreviations

ACT: Acceptance and Commitment Therapy
ASA: American Society of Anesthesiologists
CBT: Cognitive Behavioral Therapy
CVT: Clinical Video Teleconferencing
COMI: Core Outcome Measures Index
CPSP: Chronic postsurgical pain
DDD: Degenerative disc disease
EQ-5D: EuroQualityOfLife-5 dimensions
FABQpa: Fear Avoidance Beliefs Questionnaire
LBP: Low back pain
MQS: Medication Quantification Scale
NRS: Numeric Rating Scale
ODI: Oswestry Disability Index
PCS: Pain Catastrophizing Scale
PGIC: Patient’s global impression of change
PROMIS: Patient-Reported Outcomes Measurement Information System
PMR: Progressive muscle relaxation
PSQ: Pain Sensitivity Questionnaire
RCT: Randomized controlled trial
SD: Standard Deviation
SFQ: Surgical Fear Questionnaire
WPAI:LBP: Work productivity and activity impairment: low back pain
